**7. Research methodology**

- **Research design**

This study is quantitative in nature and experimental in design. Specifically, this is a parallel cluster‐randomized controlled trial (cRCT). The schools will be the unit of randomization (clusters). The trial will be used to assess the effectiveness of online life skills program in reducing mental health problems (depression, anxiety and stress) among Arabic adolescents in Klang Valley, Malaysia. There are around 18 well‐known Arabic schools in Klang Valley area, with students from different Arab countries (i.e., Yemen, Iraq, Egypt, Libya, Syrian, Saudi Arabia, and etc).

- **Study location (state and justify the exact study location)**

The study will be located in Klang Valley, in the state of Selangor, Malaysia.

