***-* Sample size estimation (to consider non-response or attrition rate)**

**Sampling size**:

The total sample size needed will be calculated by applying the formula for two population means

Means and standard deviation used for the intervention group and control group are based on the estimation offered in a previous RCT (Osborn et al., 2020). Calculation of the required sample size in this study was performed based on the guidelines in the CONSORT for cluster RCTs. By considering the account intra-class correlation coefficient (ICC), it is necessary to multiply the sample size in RCTs by design effect=1+(m–1)*ICC, where m is the average cluster size. The formula for fixed number of clusters with unequal cluster sizes will be used. Adequate sample size after Adjust for attrition rate and expected proportion eligible and multiply with design effect= 165. Therefore, the total sample size required was 165 students. Number of clusters (schools) = estimated sample size/ cluster size = 165/54=3. Following the sample size calculation, the number of schools needed will be 3 schools. However, in order to get the required sample size, a total number of 12 schools that met the inclusion and exclusion criteria during the study time will be included in the study.

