***-* Sampling method and subject recruitment**

**Sampling Method**

A cluster sampling will be used for selection of the schools. There are 12 Arabic schools in Klang Valley that meet the inclusion and exclusion criteria for this study and they will be selected to be included in the study. In order to get the required sample size, the total number of 12 schools that met the inclusion and exclusion criteria during the study time will be included in the study. Each of the schools (clusters) will then receive a serially numbered unique code. The clusters will be assigned to the intervention or control group by the ratio 1 to 1 and will be performed using block randomization using random block sizes of 2 and 4 by an independent statistician from Universiti Putra Malaysia. Therefore, 6 clusters will be in the intervention group and 6 clusters will be in the control group. Then all the students (aged 14-18 years) in the selected school, and who give assent and consent from their parents to participate will be included in the study.

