**10.** **Data analysis**

We will use SPSS Statistics version 25.0 (IBM Corp) to analyse the data. Statistical significance will be considered as a P value of less than .05. Analysis of the data will take into account clustering of students within schools. The study will use statistical analyses, including:

Descriptive analyses using the mean and standard deviation for continuous variables and the count and percentages for the dichotomous or categorical variables will be used to describe the data at baseline. Descriptive statistics of the respondents’ socio-demographic characteristics, chi-square test for nonparametric categorical variables, and the Mann-Whitney-U test was used for comparison of continuous and not normally distributed data, and 2-tailed t test for continuous variables, to compare between the control and intervention groups on socio-demographic variables and primary and secondary outcome measures. In relation to the missing data, the intention-to-treat (ITT) analysis will be used.

The effectiveness of the intervention will be assessed using the generalized estimation equation (GEE). Specifically, the differences in the research hypothesis in terms of student’s depression, anxiety and stress levels will be compared at 3 points—time 1 (pre-intervention), time 2 (immediately post-intervention), and time 3 (3-month follow-up) between and within the intervention and the control groups adjusted for covariate variables.

The GEE method will be chosen because of its efficiency in appropriately modelling the structure of the correlations of the pre-post repeated measures and its low degree of reliance on the assumption of normality in the distributions of data for the variables in the analysis. Furthermore, in the context of RCT research, multilevel models such as the GEE are the most appropriate model because they permit the estimation of treatment effects (i.e., group differences) across multiple time points within a single statistical model (Wears, 2002; Huh et al., 2012).

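### GEE at the 5% level on 12 randomised schools has a type I error of about 10% unless a small-sample method is used, and school is not named as the GEE cluster

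*Protocol*

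**What the plan says.** Protocol section 7, under Research design: "The schools will be the unit of randomization (clusters"). Under Sampling Method: "Therefore, 6 clusters will be in the intervention group and 6 clusters will be in the control group".

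Section 10 sets the level, "Statistical significance will be considered as a P value of less than .05", and names the test of effectiveness: "The effectiveness of the intervention will be assessed using the generalized estimation equation (GEE"). It compares depression, anxiety and stress at three time points, between and within groups, with covariate adjustment. One reason given for choosing GEE is "its efficiency in appropriately modelling the structure of the correlations of the pre-post repeated measures". Others are its low reliance on normality and its description as a multilevel model.

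The opening paragraph of section 10 also makes a general commitment that the analysis will allow for students being clustered in schools. The GEE paragraphs do not refer back to it. They name no subject or cluster variable and mention no adjustment for a small number of clusters. No ICC value appears anywhere in the protocol.

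**The concern.** The usual GEE inference (robust sandwich variance, Wald test against a normal or chi-square reference) is justified for a large number of independent clusters. The independent units here are schools, and there are 12. With so few, the uncorrected sandwich variance is too small on average, and the reference distribution ignores the uncertainty in that variance. Both push towards false positives.

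The second problem is which unit the GEE treats as independent. GEE has one clustering level. The correlation cited in its favour lies within the student, so an analyst following that paragraph could define the student as the subject. School, the randomised unit, would then drop out of the variance, against the section's own commitment.

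This is the only test stated for effectiveness on the primary outcomes. If its true level is about twice the stated one, an ineffective programme is declared effective too often, and the 95% confidence intervals are too narrow.

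**Working it through.** **Inputs from the protocol.** Nominal level 0.05. Two-sidedness is stated only for the baseline comparison ("2-tailed t test for continuous variables") and is assumed here for the GEE test. There are 12 schools, 6 v 6. Sample size: "Therefore, the total sample size required was 165 students". Cluster size: "Number of clusters (schools) = estimated sample size/ cluster size = 165/54=3" (165/54 = 3.06). Spread over the 12 schools actually used, 165/12 = 13.75 students per school. The protocol's design effect is 1 + (m − 1) × ICC.

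**Assumed, because the protocol does not give them.** ICC 0.01 to 0.20, cluster size m between about 14 and 54, and the stability of school effects over time.

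**1. School as the GEE cluster, uncorrected sandwich, normal reference.** With equal school sizes the sandwich divides each arm's between-school sum of squares by 6 instead of 5. The estimated variance is therefore 5/6 of the unbiased one, and the Wald statistic is a t on 10 df multiplied by √(6/5).

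- Type I error = 2 × P(t10 > 1.96 × √(5/6)) = 2 × P(t10 > 1.789) = **10.4%**. This needs no ICC and no cluster size, and it holds equally for school-mean changes.
- Simulated 1-df tests: 9% to 12% with equal sizes, 11% to 15% with a school-size CV of 0.5. The protocol itself expects unequal cluster sizes.
- Simulated joint 2-df group-by-time test: 15% to 23%.
- Correcting the variance only (normal reference kept): 2 × P(t10 > 1.96) = 7.8%.
- Correcting the reference only (t10, uncorrected sandwich): 2 × P(t10 > 2.228 × √(5/6)) = 6.9%.

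Both corrections are needed.

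**2. Student as the GEE subject, single time point.** Type I error = 2 × [1 − Φ(1.96/√DE)], with DE = 1 + (m − 1) × ICC.

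| ICC | DE, m = 13.75 | Error | DE, m = 54 | Error |
|---|---|---|---|---|
| 0.01 | 1.13 | 6.5% | 1.53 | 11.3% |
| 0.05 | 1.64 | 12.6% | 3.65 | 30.5% |
| 0.10 | 2.28 | 19.4% | 6.30 | 43.5% |
| 0.20 | 3.55 | 29.8% | 11.60 | 56.5% |

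**3. Student as the GEE subject, change from baseline.** A school effect that is constant over time cancels in the change. Simulation with 12 equal schools and ICC 0.05 gave:

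| School variance that varies over time | m = 14 | m = 54 |
|---|---|---|
| none | 5.4% | 5.1% |
| one fifth | 9.0% | 17.5% |
| one half | 12.9% | 31.0% |

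Across runs the last two rows span about 9% to 32%. A closed-form check agrees. Let f be the varying fraction and r the within-student correlation, assumed 0.5. The ICC of the change is 0.05f/[0.05f + 0.95(1 − r)]. For f = 0.5 this is 0.025/0.500 = 0.05. At m = 54, DE = 3.65 and the error is 30.5%. At m = 14, DE = 1.65 and the error is 12.7%.

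**4. Small-sample methods.** A t test on 10 df comparing school means gave 4.6% to 5.3% in simulation (m = 14 or 54, size CV 0 or 0.5, ICC 0.01 to 0.10). GEE clustered on school with the Mancl-DeRouen variance and t on 10 df gave 2.8% to 4.4% for a single follow-up contrast, which is slightly conservative.

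**The case against.** The strongest reply is that section 10 commits the whole analysis to allowing for clustering within schools. The repeated-measures sentence gives a reason for choosing GEE and does not define the subject. Variance estimator, reference distribution and subject variable are details that an analysis plan, not shown here, may settle. This stands in part. A reader might infer that the plan ignores school clustering. The document does not support that: the commitment is there but is not connected to the test. The protocol also does not say that the sandwich will be uncorrected, so the 10.4% is conditional on that choice. What remains is the protocol's own pairing of GEE at P < .05 with 6 schools per arm, which needs a small-sample method to hold its level.

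A reader might also take about 9% as a floor, or a figure such as 48% as a ceiling. Neither is supported. The rate is 7.8% with an unbiased variance and a normal reference, and 6.5% with school omitted at ICC 0.01 and 13.75 students per school. A rate of 48% needs a design effect of about 7.7, that is an ICC of 0.126 at 54 per school or about 0.53 at 13.75. Having 54 in every school means 54 × 12 = 648 students against a requirement of 165. At ICC 0.20 and 54 per school the rate exceeds 48%.

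The single-time-point figures are also not the planned analysis, which includes baseline and concerns change. That is correct, and it is why the change-contrast results are given separately. They show that the error can be nominal when school effects are stable, which the protocol gives no basis to assume.

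Calling GEE a multilevel model is inaccurate, but correcting the label would change no result.

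**Conclusion.** The point holds in this form. Effectiveness is tested by GEE at the 5% level on 12 randomised schools, and the commitment to allow for school clustering is not tied to that test. With school as the cluster, an uncorrected sandwich and a normal or chi-square reference, a 1-df test has a type I error of about 10%: 10.4% exactly for equal school sizes and normally distributed school means, 11% to 15% in simulation with unequal sizes.

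If the student is the subject, no single figure can be given. The rate runs from nominal to several times nominal, depending on the ICC, the cluster size and the stability of school effects, none of which the protocol settles. Those ranges rest on assumed values. The 10.4% rests only on the 6 v 6 design and the uncorrected large-sample test.

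**What to change.** In section 10, state one of the following for the primary comparison:

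- **GEE retained.** School is the GEE subject. The sandwich variance is corrected for few clusters, for example by Mancl-DeRouen. The arm and arm-by-time contrasts are referred to t with 12 − 2 = 10 df.
- **School-level analysis.** The arm difference in school mean change is tested with a t test on 10 df.
- **Mixed model.** Random intercepts for school and student, plus a random school-by-time term, with small-sample degrees of freedom. Intercepts alone are not enough. In simulation of the change contrast with one fifth or one half of the school variance varying over time, the intercept-only model gave 8.3% and 12.3% at 14 per school, and 17.2% and 30.6% at 54.

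The cost is a changed analysis paragraph and possibly a procedure outside SPSS 25, which section 10 names; whether that version offers the corrected variance was not checked. P-values will be somewhat larger. For equal school sizes, intervals widen relative to the uncorrected sandwich by (2.228/1.960) × √(6/5) = 1.245, about a quarter. No new data are needed.

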**11. Expected outcome**

**Primary outcome measure**

A change in the mean score of the Mental Health problems (Depression, anxiety and stress). It is expected that the education program will be effective in reducing the level of depression, anxiety and stress.

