**5. Research Question(s)**

What is the effect of online Life Skills-based intervention on depression, anxiety and stress levels, self-efficacy and coping skills between and within the intervention and control groups immediately post-intervention, and 3 months after the intervention and even after adjusted for covariate variables?

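### The primary outcome covers three DASS-21 scales at two post-intervention times, with no primary time point, no success rule and one P<.05 threshold

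*Protocol*

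**What the plan says.** The primary outcome (protocol section 11, Primary outcome measure) is "A change in the mean score of the Mental Health problems (Depression, anxiety and stress"). Section 10 (Data analysis) names the same three constructs for the GEE: "depression, anxiety and stress levels will be compared at 3 points". The three points are baseline, then "time 2 (immediately post-intervention), and time 3 (3-month follow-up) between and within the intervention and the control groups". The research question in section 5 also asks about both later times, "immediately post-intervention, and 3 months after the intervention", and ranks neither.

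The only decision rule is in section 10: "Statistical significance will be considered as a P value of less than .05". It applies to everything, with no split or ordering. A two-sided test is stated only for the "2-tailed t test for continuous variables"; the GEE contrasts carry no statement of sidedness.

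The protocol does not rank the scales, define a total score, or say whether one, some or all of the scales must improve for the programme to be called effective.

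**The concern.** A primary outcome should fix what is measured, when, and what result counts as success. Here the first is loosely worded and the other two are missing. Three scales at two times make six between-arm comparisons of equal standing, each judged at .05.

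Two things are at stake. First, if success may be claimed on whichever comparison is significant, .05 is the error rate of each comparison and not of the trial's conclusion. Second, with time point and scale left open, the favourable result can be chosen after the data are seen, and the protocol would not contradict that choice.

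**Working it through.** **The plan's own figure.** The protocol states no error rate for the primary conclusion; its only error figure is the .05 threshold. The sample-size paragraph in section 7 arrives at 165 students but gives no difference, SD, power, ICC, attrition or eligible proportion. It therefore cannot be rebuilt and does not show which scale or time it was meant to power.

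**Inputs from the protocol.** Threshold .05 (section 10); three scales (sections 10 and 11); two post-intervention times (sections 5 and 10).

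**Assumptions.** All null hypotheses are true. Tests are two-sided with |Z| > 1.96. Any one significant result counts as success. The correlation between test statistics is not given, so it is varied from 0 to 0.8, both between scales and between times.

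**Independent tests.** The chance of at least one false positive in k tests is 1 − 0.95^k:
- k = 6 (three scales, two times): 1 − 0.95^6 = 0.265
- k = 3 (one test per scale): 1 − 0.95^3 = 0.143
- k = 2 (one total score, two times): 1 − 0.95^2 = 0.0975

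Counting only results that favour the programme, each test has a 2.5% tail, so six give 1 − 0.975^6 = 0.141.

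**Correlated tests.** The statistics were simulated as multivariate normal. For six tests the correlation matrix is the Kronecker product of a 3×3 exchangeable matrix (scales) and a 2×2 matrix (times), with the same correlation in each.

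| Correlation | Six tests, either direction | Six tests, benefit only | Three tests, either direction | Two tests, either direction |
|---|---|---|---|---|
| 0 | 26.5% | 14.1% | 14.3% | 9.75% |
| 0.5 | 21.9% | 11.0% | 12.6% | 9.1% |
| 0.7 | 17.7% | 8.8% | 10.9% | 8.3% |
| 0.8 | 14.9% | 7.5% | 9.8% | 7.8% |

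The nominal level is 5% in the either-direction columns and 2.5% in the benefit-only column. Every entry is above it.

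**Not counted.** The within-group comparisons are left out. So are the t and Mann-Whitney tests that section 10 also lists for the outcome measures, which may be meant for baseline only.

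**After the fix.** With three scales at one time, Holm's procedure compares the ordered P values with .05/3 = .0167, .05/2 = .025 and .05. It holds the familywise error at or below .05 whatever the correlation.

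**Power cost, by illustration.** A test with an assumed 80% power at two-sided .05 has a standardised mean of 1.96 + 0.84 = 2.80. At .0167 the critical value is 2.39, so power is Φ(2.80 − 2.39) ≈ 66%. This is the worst case under Holm, because the later steps use larger thresholds.

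**The case against.** The strongest reply is that the protocol nowhere says one significant result out of six is enough. Section 11 expects a reduction in depression, anxiety and stress together. If all three had to improve at one time, the chance of a false claim of benefit would be only about 0.2% to 0.4% at correlations of 0.5 to 0.7. Section 10 speaks of effects across times in a single model, which could mean one group-by-time test per scale. Section 11 refers to the mean score in the singular, which could mean one total. All of this stands as evidence that the text is open to several readings. It does not settle the matter, because the protocol adopts none of them. Separate scales are the more natural reading: section 7 (Research tools) screens on depression, anxiety or stress, and no total is defined.

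A reader might infer that the trial's false-positive rate is about 18% to 22%. The documents do not support that as a single figure. It requires six separate tests, any one counting, correlations of about 0.5 to 0.7, and findings of harm counted with findings of benefit. At those correlations, false claims of benefit alone are about 9% to 11%.

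A reader might also infer that no adjustment will be made. The protocol does not establish that: the adjustment method is often left to a statistical analysis plan, and one may exist that is not shown. The primary time point and the meaning of success belong in the protocol, however, and a blanket .05 over unranked primary comparisons is a stated rule.

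Nor can extra error from a GEE with 12 schools simply be added to these figures. It is not quantified here, and error rates do not add in that way.

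Finally, section 11 mentions informing the feasibility of later full-scale trials. That does not remove the point, since the same section and section 7 also aim at effectiveness and section 10 sets a significance test.

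**Conclusion.** The concern holds in a limited form. The protocol leaves the primary time point and the success criterion unspecified and applies one .05 threshold to all the primary comparisons. If any significant scale at either time is taken as success, the error rate of the primary conclusion is above the stated level. The excess depends on the reading: largest for six separate tests, smaller for one test per scale, smallest for a single total at two times. The figures rest on true nulls, on that success rule and on assumed correlations, and should be reported with those assumptions. The direction does not depend on the correlation within the range examined; it would reverse only if all scales were required to improve, which the protocol does not say. The defect is worth correcting before analysis but does not invalidate the design.

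**What to change.** In sections 10 and 11:

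1. Name one post-intervention time as primary and justify it. Three months is one option, but nothing in the documents favours it over the immediate assessment, so the sponsor must give the reason.
2. State that depression, anxiety and stress are scored and tested separately.
3. Test the three between-arm differences at that time with Holm's procedure at an overall two-sided .05, and claim an effect only on the scales that pass.
4. Make the other time secondary, alongside self-efficacy and coping.

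This takes a few sentences and changes no data collection. The statistical cost is the stricter first threshold of .0167, with the power loss illustrated above. The actual loss cannot be worked out from the protocol because the sample-size inputs are not given, so the sponsor should check the 165 students against the chosen rule.

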**Secondary outcome measure:**

• Increase the self-efficacy mean score and the coping skills mean score among Arabic secondary school students.

This trial is expected to provide valuable insight into the implementation and effectiveness of online Life Skills educational programs in reducing depression, anxiety and stress levels among Arabic adolescents and improving their behaviours. The aim of designing the initial cluster RCT is also to provide information regarding the feasibility of potential future full-scale trials in order to optimize the intervention and design approach. Process evaluation outcomes will provide contextual information about implementation decisions of Arabic student immigrants, researchers, and higher education stakeholders.

